**Sequential versus quadruple therapy as second- line treatment after failure of standard therapy for Helicobacter pylori infection**

Study protocol

Protocol summary

| 1. PPI( Lansoprazole 30mg x2/day) + amoxicillin 1gx2/day followed by 5 days of PPI(Lansoprazole 30mg x2/day) + two antimicrobial drugs ( Clarithromycin500mg x2/day and Tinidazole 500mg x2/day )  2. quadruple drug regimen (i.e.-14 days of PPI (Lansoprazole 30mg x2/day) + Bismuth Subsalicilate 525mg X4/day + Metronidazole 500mg x3/day + Tetracycline 500mg x4/day or Doxyllin 100mg x2/day ) | Regimens |
| --- | --- |
| Both treatments are approved for the eradication of Helicobacter Pylori | Regulatory status |
| Prospective, randomized, open label trial | Study design |
| The objective is to evaluate the efficacy of sequential therapy, i.e. 5 days of PPI + amoxicillin followed by 5 days of PPI + two antimicrobial drugs( clarithromycin and tinidazole ) versus quadruple drug regimen( i.e.-14 days of PPI+ bismuth + metronidazole + tetracycline ) as second line treatment for Helicobacter pylori eradication | Objective |
| From world experience successful eradication on second line treatment with quadruple therapy is approximately 75 %. We assume a non-inferior eradication rate with second line therapy based on sequential therapy.  In addition we assume better compliance rate (defined as the use of >80% of the prescribed medications) in patients randomized to sequential therapy. | Study hypotheses |
| We are planning to include 258 patients of The Department of Gastroenterology, Soroka Medical Center, and Beer-Sheva, Israel. The study will include consecutive ambulatory patients assessed at Gastroenterological Department, Soroka and family practitioner, who failed standard first line therapy-triple therapy of H.pylori and have indications for eradication of H. pylori. Patients are considered initial treatment failures if histology, rapid urease, 13C-urea breath testing or stool AG test will remain positive despite first-line PPI-based triple therapy. These subjects will be randomized at a 1:1 ratio, by blocks of four. | Number of subjects |

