| The primary end points of the study are:   - The eradication rate after second line treatment based on sequential therapy comparative to eradication rate after second line therapy based on quadriple regimen. H.pylori eradication is defined as a negative C-urea breath test beginning 4 weeks after eradication treatment completion. - Rate of compliance to the prescribed therapy (more than 80% of medications used for all medications) | Primary endpoints and measurement |
| Study follow-up period will be 8 weeks. During these 8 weeks the study subjects will be assessed 3 times. | Study follow up |
| The secondary end points:  Adverse effects of sequential and quadruple treatment (taste alteration , peripheral neuropathy, seizures, nausea, vomiting, diarrhea, abdominal pain, allergic reaction, photo sensibility) | Secondary endpoints |
| The sample size calculations will be performed based on the following assumptions:  **Efficacy:**  -Rate of successfully achieved eradication of H.pylori for the standard quadruple therapy is 75%  -Non-inferiority delta of 15%  -Alpha 0.05(one-sided)  -Power 80%  Group sample sizes of 116 and 116 achieve 80% power to detect a statistically significant difference in achieving eradication of H.pylori following the recurrent infection. To accommodate a 10% rate of lost to follow-up we will enroll 258 subjects  **Compliance:**   - In standard therapy group compliance rate is expected to be 60% - We anticipate that in sequential therapy group the compliance rate will be 80%.   With two-sided alpha of 0.05 we have 89% power to detect a significant difference. | Sample size consideration |
| 1.signed informed consent  2.age at least 18 years  3. persisting *H.pylori* infection after at least one course of first-line standard triple therapy (Moxypen, Clarin or Flagyl based) | inclusion criteria |
| 1) history of gastrectomy  2) gastric malignancy, including adenocarcinoma and lymphoma  3) previous allergic reaction to antibiotics (amoxicillin, clarithromycin, metronidazole, tetracycline) and proton pump inhibitors  4) Active upper gastrointestinal bleeding within the previous 1 week  5) contraindications to the treatment drugs  6) Pregnant or lactating women  7) Severe concurrent disease or malignancy | Exclusion criteria |
| [name] , Gastroenterology Department, Soroka Medical Center | Principal study investigator |
| Soroka Clinical Research Center  Head: [name] MD PhD  Email: [contact] | Data management and analysis |

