Primary objectives of this study is to compare safety and effectiveness of the eradication rate after second line treatment based on sequential therapy comparative to eradication rate after second line therapy based on quadruple regimen .

Primary endpoint: H. pylori negative breath test starting 4 weeks after the completion of the treatment.

The secondary end points are the adverse effects of sequential and quadruple treatment (taste alteration, peripheral neuropathy, seizures, nausea, vomiting, diarrhea, abdominal pain, allergic reaction, and photosensitivity) and patient compliance with it. Compliance is considered to be satisfactory when drug intake exceeded 80%.

We are planning to include 258 patients of The Department of Gastroenterology, Soroka Medical Center, Beer-Sheva, Israel. Also we will include at ambulatory patients - with direct referral from family physician or newspaper publicity .

Inclusion criteria are:

1) Age at least 18 years

2) Persisting *H. pylori* infection after at least one course of first-line PPI–Amoxicillin–Clarithromycin or Metronidazole therapy. Patients are considered initial treatment failures if histology, rapid urease, stool Ag or 13C-urea breath testing will remain positive despite first-line PPI-based triple therapy. These tests should be performed during the one year before enrollment in this study.

Exclusion criteria:

1) Age< 18

2) History of gastrectomy

3) Gastric malignancy, including adenocarcinoma and lymphoma

4) Previous allergic reaction to antibiotics (amoxicillin, clarithromycin, metronidazole, and tetracycline) and proton pump inhibitors

5) Active upper gastrointestinal bleeding within the previous 1 week

6) Contraindications to the treatment drugs

7) Pregnant or lactating women

8) Severe concurrent disease or malignancy.

Written informed consent will be obtained from all patients prior to enrolment.

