The 258 patients enrolled will be randomized to receive one of the following two treatment regimens for10/ 14 days the patients will be informed of the importance of full compliance, warned of side-effects, instructed to complete treatment, and provided with a contact number, in case of problems. One week after completing these therapies, compliance will be evaluated by a physician during the visit in clinic by direct questioning or pill counting. Compliance is considered to be satisfactory when drug intake exceeded 80%. In addition, at this time all patients will be interviewed for adverse events. *H. pylori* eradication is defined as a negative 13C-urea breath 4-16 weeks after eradication treatment completion [[17](http://www3.interscience.wiley.com/cgi-bin/fulltext/118536283/main.html,ftx_abs" \l "b17%23b17)]. (C-urea breath test- Patients are fasted for 4 h before testing. No test meal will be given, and a pre-dose breath sample is obtained. 75 mg of 13C-urea powder dissolved in 50 mL of water is then administered orally, and a second breath sample is collected 30 minutes later. Collected samples are analyzed using an isotope ratio mass spectrometer). The patient should stop receiving PPI for 10 days before the breath test and not receive any antibiotics for 7days before this exam.

Subject screening and treatment flowchart

Ambulatory patients who failed standard triple first line therapy of H.pylori

Obtain informed consent

Enroll and randomize subjects in two Strata:

1-standard quadruple therapy

2- Sequential therapy

Following drug treatment

For standard quadruple therapy-14 days

For sequential therapy-10 days

First evaluation at one week after completing these therapies

Visit in ambulatory clinic and check

Compliance with treatment and reports of adverse effects

Compliance> 80%-

satisfactory

Compliance < 80% -

Unsatisfactory

Second evaluation -8 weeks after completing treatment

C-urea breath test check the results of

Schedule of events

|  | On enrollment | 7 days after completing treatment –visit in clinic | 8 weeks after completing treatment |
| --- | --- | --- | --- |
| Sign informed consent | X |  |  |
| Check inclusion/exclusion criteria | X |  |  |
| Start one of two treatment regimen  ( sequential or quadruple) | X |  |  |
| Check compliance |  | X |  |
| Ask about adverse effects |  | X |  |
| c-urea breath test |  |  | X |
|  |  |  |  |
|  |  |  |  |

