**3.5 Baseline Procedures**

Ambulatory patients who failed standard triple first line H. pylori eradication therapy will be approached by a member of the study research team. A study research staff member will explain the purpose, procedures and intent of the study to each potential participant. Interested subjects will be invited to join the study and asked to provide a written informed consent prior to initiation of any study-related procedure.

*Enrollment*

Subjects who failed to meet the clinical inclusion and exclusion criteria will not be included in the study. Eligible subjects will be randomized to one of the two treatment arms in a1:1 ratio sequential therapy and quadruple therapy, by blocks of four.

*7 days after completing treatment*

First evaluation will take place one week after completing the treatment. A study research staff member will ask each patient about the compliance and adverse effect .

*4 weeks after completing treatment*

Starting with Four weeks after completing treatment and till 16 week C-urea breath test will be performed

*8 weeks after completing treatment*

Eight weeks after completing treatment the results of C-urea breath will be checked

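### No symptoms are recorded at enrolment, so pre-existing nausea, vomiting, diarrhoea or abdominal pain may be counted as adverse effects and dilute the tolerability comparison

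*Protocol*

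**What the plan says.** The Methods section lists the adverse effects that make up the secondary endpoint: "taste alteration, peripheral neuropathy, seizures, nausea, vomiting, diarrhea, abdominal pain, allergic reaction, and photosensitivity". The protocol summary gives the same nine. The study objectives also mention safety: "Primary objectives of this study is to compare safety and effectiveness of the eradication rate".

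Three places fix when these effects are asked about, and they agree:

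- The schedule of events marks only the column for 7 days after treatment: "Ask about adverse effects | | X".
- The Methods text, describing the visit one week after treatment, says: "In addition, at this time all patients will be interviewed for adverse events".
- Section 3.5, under the heading for 7 days after treatment, says: "A study research staff member will ask each patient about the compliance and adverse effect".

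At enrolment the schedule has three entries: consent, the eligibility check ("Check inclusion/exclusion criteria | X") and the start of treatment. Section 3.5 deals with baseline procedures but names no symptom record. Nothing in the protocol says whether an effect must be new or worse than before treatment to count.

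**The concern.** The trial recruits patients "who failed standard first line therapy-triple therapy of H.pylori and have indications for eradication of H. pylori", and the Background links the infection to chronic gastritis and peptic ulcer. It is plausible that some of them already have abdominal pain, nausea, vomiting or diarrhoea at entry. With a single interview after treatment and nothing recorded before it, a complaint the patient brought into the trial can be told from a new one only by asking the patient to recall when it began. The trial is open label, so patients and staff may both know the arm when that judgement is made.

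At stake is the tolerability comparison. The Background gives side effects and complicated dosing as the main reasons for poor adherence to quadruple therapy, and it calls for better tolerated alternatives. Background symptoms counted in both arms raise both rates and narrow the gap between them.

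An analysis plan can define a treatment-emergent effect, but it cannot supply baseline data that were never collected. Whether they are collected is settled by the schedule of events, which is in this document.

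**Working it through.** The protocol states no rate, difference or power for adverse effects, so there is no figure to reproduce. The calculation below is an illustration.

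**Inputs**

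- From the protocol: 258 enrolled, 1:1 allocation, so n = 129 per arm.
- Assumed: new-onset rates of one symptom r = 10% in one arm and 20% in the other; two-sided alpha 0.05.
- Assumed: baseline prevalence b of that symptom, equal in both arms as randomisation gives in expectation, at 5%, 15% and 30%.
- Worst case: every patient with the symptom at entry still has it and reports it as an adverse effect.

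**Formulas**

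- Observed rate if pre-existing symptoms are counted: p = b + (1 − b)r.
- SE = √{[p₁(1 − p₁) + p₂(1 − p₂)]/n}; power = Φ(d/SE − 1.96), where d = p₂ − p₁.
- New onset among patients free of the symptom at entry: rates stay at 10% and 20%, and n becomes 129(1 − b).

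**If pre-existing symptoms are counted**

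- b = 5%: 14.5% v 24%, d = 0.095, SE = √(0.306375/129) = 0.0487, power = Φ(−0.01) ≈ 50%.
- b = 15%: 23.5% v 32%, d = 0.085, SE = √(0.397375/129) = 0.0555, power = Φ(−0.43) ≈ 33%.
- b = 30%: 37% v 44%, d = 0.07, SE = √(0.4795/129) = 0.0610, power = Φ(−0.81) ≈ 21%.

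**If only new onset among symptom-free patients is counted**

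- b = 5%: n = 122.6, SE = √(0.25/122.6) = 0.0452, power = Φ(0.25) ≈ 60%.
- b = 15%: n = 109.7, SE = √(0.25/109.7) = 0.0477, power = Φ(0.13) ≈ 55%.
- b = 30%: n = 90.3, SE = √(0.25/90.3) = 0.0526, power = Φ(−0.06) ≈ 48%.

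The avoidable loss is thus about 10 points of power at 5% prevalence, 22 at 15% and 27 at 30%. It vanishes at b = 0, where both ways of counting give 10% v 20%, SE 0.0440 and power of about 62%.

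**Sensitivity to the assumed rates and n.** With 10% v 25% and the protocol's 116 evaluable per arm (power by a pooled-variance formula), counting pre-existing symptoms gives 65%, 49% and 37% at prevalences of 10%, 20% and 30%. Counting only new onset gives 82%, 77% and 72%. The pattern is the same.

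**The case against.** A reader might infer that the protocol scores pre-existing symptoms as drug effects. It does not say so. The endpoint is worded as effects of treatment, staff ask about adverse effects rather than any symptom present, and an interviewer could ask whether a complaint began or worsened on treatment. That objection stands. What the protocol leaves open is how the separation is made; it has no record from before allocation to rest on.

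A reader might also infer that one arm is favoured. Counting background symptoms does not do that. Under 1:1 randomisation they balance in expectation, so the effect is dilution. Attribution by people who know the arm is a separate matter, and a baseline checklist does not remove it from the later interview.

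A third tempting reading is that power falls from 62% to 21%. The 62% belongs to a trial in which nobody has the symptom at entry, and no change to the schedule can deliver that. At 30% prevalence the fair comparison is 21% against about 48%.

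Other points also stand. The protocol gives no prevalence of symptoms at entry, and patients may come through family physicians or newspaper publicity, so prevalence could be low. Full persistence and reporting of baseline symptoms is a worst case. Five of the nine effects are outside the argument. Adverse effects are a secondary endpoint with no hypothesis or power claim. Safety appears in the primary objective, but the primary endpoint stated directly below it is the breath test.

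Two counter-arguments do not carry. A definition of treatment-emergent effects could sit in the analysis plan or the case report form, but neither replaces data absent from the schedule. Section 3.6 foresees review of hospital charts and office records, yet it names no symptom item, and referred or self-presenting patients cannot be assumed to have a uniform, recent record.

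**Conclusion.** The point holds as a limited one. The schedule, the Methods text and section 3.5 together provide one post-treatment inquiry and no symptom record at enrolment. Pre-existing complaints of the four gastrointestinal kinds may therefore be counted, or be set apart only by unblinded recall.

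On the stated assumptions, counting them leaves power at about 33% rather than 55% for 15% prevalence, and at about 21% rather than 48% for 30%. These figures rest on assumed rates and on the worst case for persistence and reporting. With low prevalence, or careful questioning about onset, the loss is small.

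Only the comparison of a secondary endpoint is affected. This is a cheap improvement worth making and does not threaten the trial's main conclusions.

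**What to change.** In the schedule of events, add an enrolment mark for a short checklist giving presence and severity of each of the nine listed effects, completed before the allocation is known. Add the same step to the enrolment paragraph of section 3.5. Repeat the identical checklist at the 7-day visit, and define the secondary endpoint as an effect that is new or worse than at enrolment.

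The cost is one extra eCRF page and a few minutes at an existing visit, with no new visit or procedure. Patients who have already started treatment cannot be given a prospective baseline, so the change helps only those enrolled after it.

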**Screening Procedures**

Prior to subject participation in this study, the Investigator must obtain written Ethics Committee (EC) and other local regulatory bodies as appropriate approval for the protocol and the informed consent form. The approved consent form should clearly reflect the EC approval date.

Failure to obtain a signed and hand dated informed consent prior to the procedure constitutes a protocol violation, which is reportable to the EC.

**3.5 Baseline Procedures**

Ambulatory patients who failed standard triple first line H. pylori eradication therapy will be approached by a member of the study research team. A study research staff member will explain the purpose, procedures and intent of the study to each potential participant. Interested subjects will be invited to join the study and asked to provide a written informed consent prior to initiation of any study-related procedure.

*Enrollment*

Subjects who failed to meet the clinical inclusion and exclusion criteria will not be included in the study. Eligible subjects will be randomized to one of the two treatment arms in a1:1 ratio sequential therapy and quadruple therapy, by blocks of four.

*7 days after completing treatment*

First evaluation will take place one week after completing the treatment. A study research staff member will ask each patient about the compliance and adverse effect .

*4 weeks after completing treatment*

Starting with Four weeks after completing treatment and till 16 week C-urea breath test will be performed

*8 weeks after completing treatment*

Eight weeks after completing treatment the results of C-urea breath will be checked

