|  | Study monitor |
| Soroka Medical Center, Beer Sheva, Israel | Study site |
| 07/2011  The enrollment is planned to continue for 18 months | Estimated start data and enrollment phase |
|  |  |

Background

Helicobacter pylori s known to play a major contributory role in the pathogeneses of chronic gastritis, peptic ulcers, and gastric malignancies (1). Consequently, great emphasis has been placed on its successful eradication. Many first-line treatments have been employed for this purpose, and the most successful regimens have achieved eradication rates of 75–90% [[2](http://www3.interscience.wiley.com/cgi-bin/fulltext/118536283/main.html,ftx_abs" \l "b2%23b2)].in Israel- in period of 2003-2007- eradication rate-from different sources- was between 57.5-82 %.(18) Treatment of *H pylori* infection is a common problem in many practice settings. The prevalence of *H. pylori* infection has been falling in developed countries bud difficulties with eradication have been increasing as the prevalence of resistant strains of *H.pylori* increase. In Israel during the period of 2002-2006 rate of resistance rise- for metronidazole- 31.4% to 60%-(18)' for clarithromycin- resistance rare in the same period is -8% -65%.(18). Another major problem with antimicrobial treatment regimens for *H. pylori* is adherence with the treatment regimen. Intolerable side-effects with prolonged course of treatment can lead to premature discontinuation of therapy and the development of resistant strains of *H.pylori*. (19). Patients with persistent H. pylori infection, despite antibiotic therapy, present a greater challenge with respect to successful cure [[3](http://www3.interscience.wiley.com/cgi-bin/fulltext/118536283/main.html,ftx_abs" \l "b3%23b3)].

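### A single fixed block size of four, stated in the protocol of an open-label trial with one named site, could let a recruiter know up to one third of upcoming allocations

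*Protocol*

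**What the plan says.** The allocation rule appears twice. Section 3.5 (Enrollment) reads: "Eligible subjects will be randomized to one of the two treatment arms in a1:1 ratio sequential therapy and quadruple therapy, by blocks of four". The Number of subjects row of the protocol summary reads: "These subjects will be randomized at a 1:1 ratio, by blocks of four". Both give one block size, and neither says that it varies or is withheld from the staff who recruit.

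The features that make the block size informative are stated elsewhere in the protocol:

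- The Study design row describes a "Prospective, randomized, open label trial", so each allocation is visible once treatment starts.
- The Study site row names one place: "Soroka Medical Center, Beer Sheva, Israel".
- No baseline stratification factor is given. The flowchart says "Enroll and randomize subjects in two Strata", but the two items listed beneath are the two treatment arms.
- Section 3.5 says that potential participants "will be approached by a member of the study research team".
- The Sample size consideration row expects compliance of 60% on standard quadruple therapy and 80% on sequential therapy.
- The Number of subjects row says that consecutive ambulatory patients will be included.

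**The concern.** In a 1:1 block of four, each arm appears exactly twice. Someone who knows the block size and has followed the sequence can count what is left. Once one arm has been used twice, every remaining place in that block belongs to the other arm. Concealing the list does not prevent this, because the prediction uses only past allocations and the published block size.

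The staff also have a stated reason to act on the knowledge. The protocol expects poorer compliance with quadruple therapy, and its Background attributes this to side effects and complicated dosing. A recruiter who foresees the next arm could approach a patient sooner, later or not at all. The arms could then differ in expected compliance or prognosis before treatment starts.

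Compliance is a primary endpoint in the summary (a secondary one in Methods), and the Background names noncompliance as a major cause of failure of quadruple therapy. Selective enrolment could therefore affect both the compliance comparison and the non-inferiority comparison of eradication. The direction cannot be told from the documents, since it depends on which patients are steered to which arm.

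**Working it through.** **Inputs.** Block size 4 and ratio 1:1 (protocol summary and section 3.5); total 258, eradication 75%, margin 15 points, one-sided alpha 0.05, power 80%, 10% loss to follow-up (Sample size consideration row).

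**The plan's own figure.** The protocol gives no predictability figure, but its total can be reproduced.

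- Without continuity correction: n = 2 × 0.75 × 0.25 × (z₀.₉₅ + z₀.₈₀)² / 0.15² = 103.04 per arm.
- With continuity correction: 103.04/4 × [1 + √(1 + 4/(103.04 × 0.15))]² = 115.99, so 116 per arm.
- Total: 2 × 116 = 232, and 232/0.9 = 257.8, so 258.

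The sample size is not in question here.

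**Allocations known with certainty.** Six orderings of a block are equally likely: AABB, ABAB, ABBA, BBAA, BABA, BAAB.

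- Positions 1 and 2 are never determined.
- Position 3 is determined when the first two match (AABB, BBAA): 2/6 = 1/3.
- Position 4 is always determined.
- Expected number per block: 1/3 + 1 = 4/3. As a share: (4/3)/4 = 33.3%.

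The total is 258 = 64 × 4 + 2, and the last two patients fill positions 1 and 2. The expected number is 64 × 4/3 = 85.3, or 85.3/258 = 33.1%.

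**Best guess.** An observer who always names the arm with more places left is right with probability 1/2, 2/3, 2/3 and 1 at the four positions. The mean is (17/6)/4 = 70.8%. Over 258 patients: 64 × 17/6 + 1/2 + 2/3 = 182.5, or 70.7%.

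**The alternative.** Block sizes are drawn at random from an assumed set. The observer knows the set but not the order of sizes, and tracks every past allocation (simulation, 400 trials of 258 patients).

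| Scheme | Certain | Best guess correct |
| --- | --- | --- |
| Fixed 4 | 33.3% (exact, full blocks) | 70.8% (exact, full blocks) |
| 4 and 6 at random | about 5.4% | about 69.3% |
| 4, 6 and 8 at random | about 2.1% | about 68.0% |

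A second simulation gave 5.6% and 2.4% certain for the two varying schemes, so the range to carry forward is about 2–6%.

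**What full use of the certain allocations could do (an assumption, not from the documents).** Suppose likely successes were placed in every certain slot of one arm and likely failures in every certain slot of the other. The arm difference would shift by one third of the gap in success rate between these two kinds of patient: 3.3, 6.7 or 10 points for gaps of 10, 20 or 30. The margin is 15 points. Partial use scales this down, and acting on probable guesses as well would add to it.

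**The case against.** Several points on the other side have weight.

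- **One third is a ceiling.** It requires a recruiter who knows the block size, has seen every allocation in order and tracks the block boundaries. The protocol speaks only of a member of the research team and does not say that one person sees the whole sequence. Patients also come through family practitioners and newspaper publicity, and nothing shows that referrers see it. A reader might infer that recruiters will know a third of allocations, but the documents support only that they could know up to a third. That recruiters have read the protocol is an inference, though an ordinary one.
- **Consecutive enrolment is stated.** If followed, it limits delaying or declining patients. This stands as a mitigation, but the protocol describes no safeguard to enforce it, and the mixed referral routes leave room over timing.
- **Consent already precedes randomisation in the flowchart, and only eligible subjects are randomised.** This is true, but prediction can act before a patient is approached.
- **The breath test is read by instrument.** That protects the measurement of eradication, not the comparability of the arms.
- **Varying the blocks barely reduces guessing.** This stands. It is tempting to set 70.8% against 50%, but 50% belongs to simple randomisation. Varying blocks reach only about 68–69%. Their gain lies in removing nearly all certain knowledge.
- **More than one site?** Section 3.6 refers to all sites, but about access to the data system. No second site is named.

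**Conclusion.** The point holds as a weakness in a stated design rule, not as a contradiction or an arithmetic error in the protocol. Fixed, disclosed blocks of four make up to one third of allocations (about 85 of 258) certain for an observer who knows the block size and has seen all earlier allocations. A single list, implied by one named site without stratification, and open treatment make that observer plausible. They do not establish that one exists.

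A reader might go further and infer that the arms will be or have been biased. The documents do not support that. They show an opening and a stated expectation about compliance that could motivate its use. The shift in the result depends on a prognostic gap and a degree of steering that the documents do not give. A change is still worthwhile, because it is inexpensive and an imbalance created at enrolment is hard to repair in the analysis.

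**What to change.** In both places (the Number of subjects row and section 3.5, Enrollment), replace the reference to blocks of four with 1:1 allocation by randomly permuted blocks of varying size. State that the sizes are known only to the data-management centre, and do not print them in the protocol. Add that each allocation is released only after the patient's consent and eligibility have been recorded.

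The costs are modest. The list has to be regenerated. The arms may end unequal by at most half the largest block, which is four patients if the largest assumed size is 8. The sample size does not change. If allocations are released electronically, more work is needed: section 3.6 describes a web system for data capture whose database is still to be developed, and no randomisation function is mentioned. That function would have to be specified and built, so it should not be counted as a small adjustment to an existing tool.

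The change removes most certain knowledge but leaves best-guess accuracy near 68–69%, and it helps only for patients allocated after it takes effect.

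### Adverse effects are collected by interview from staff who will in practice know the arm, and the protocol asks for neither severity nor reason for stopping a drug

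*Protocol*

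**What the plan says.** The Study design row of the Protocol summary reads "Prospective, randomized, open label trial". No masked interviewer or assessor is described.

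Adverse effects are collected once, at the clinic visit seven days after the end of treatment. Section 3.5 says "A study research staff member will ask each patient about the compliance and adverse effect". The Methods text says of the same visit that "compliance will be evaluated by a physician during the visit in clinic by direct questioning or pill counting", and then that "at this time all patients will be interviewed for adverse events". The Schedule of events has one row for asking about adverse effects, at that visit only. No form, diary or common wording is named.

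The Secondary endpoints row and the Methods list nine effects. Neither mentions severity or action taken. Compliance is classed as satisfactory above 80% intake, and no reason for missed drug is requested.

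On purpose, the Background says "Intolerable side-effects with prolonged course of treatment can lead to premature discontinuation of therapy" and attributes poor compliance with quadruple therapy mainly to its side effects and complicated dosing. The Study hypotheses row assumes better compliance with sequential therapy. The Methods begin "Primary objectives of this study is to compare safety and effectiveness", so safety is part of the stated primary objective.

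**The concern.** Two features of the collection method weaken the tolerability comparison.

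The first is who asks, and how. An unscripted interview lets the questioner probe harder, or accept a vaguer answer, in one arm than in the other. That matters most for symptoms known only from the patient's account, such as nausea, abdominal pain or altered taste. Here the interviewer can know the arm, and the protocol has announced which regimen it expects patients to tolerate less well.

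The second is what is asked. The problem described in the Background is effects bad enough to make patients stop. The protocol lists effects and measures intake, but asks for nothing that joins the two: neither how severe an effect was nor whether a drug was stopped because of it. If these items are not asked at the visit, no later analysis can recover them.

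At stake is whether a difference in adverse-effect rates can be read as a difference between regimens, and whether a difference in compliance can be explained by tolerability.

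**Working it through.** The protocol gives no figure for adverse-effect rates, so there is none to reproduce. The check sets the passages side by side, then illustrates scale on assumed values.

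**1. Would the interviewer know the arm?** The protocol does not say so; it is an inference. Three things support it. The trial is open label. Compliance with the assigned drugs is assessed at the same visit, by questioning or by counting pills. The visit is timed from the end of treatment, so it falls at about day 10 + 7 = 17 from the start for sequential therapy and day 14 + 7 = 21 for quadruple therapy.

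**2. Is there a stated expectation?** Yes. The Study hypotheses row and the Background together favour sequential therapy on compliance and describe side effects as a main reason for poor compliance with quadruple therapy.

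**3. Can the trial link adverse effects to missed drug?** In part. Both are collected in the same patients at the same visit, so each effect can be cross-tabulated against intake above or below 80%. The Background, however, names two causes of poor compliance with quadruple therapy: side effects and complicated dosing. A patient with nausea and low intake fits either, and the table cannot separate them. The protocol's planning rates give the number of patients concerned. With 116 per arm, unsatisfactory intake is expected in (1 − 0.60) × 116 ≈ 46 quadruple and (1 − 0.80) × 116 ≈ 23 sequential patients. For none of these does the protocol ask for a reason.

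**4. Illustration of differential questioning.** Assumed, not from the document: the true rate *r* of an effect is the same in both arms; 90% of events are elicited in the quadruple arm and a smaller share *s* in the sequential arm; the arms are compared by a two-proportion z test at two-sided 0.05, which the protocol does not state. From the protocol: *n* = 116 per arm, the evaluable number after its 10% loss.

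Observed rates are p₁ = 0.90 *r* and p₂ = *s r*. With p̄ = (p₁ + p₂)/2, SE₀ = √(2p̄(1 − p̄)/n) and SE₁ = √((p₁(1 − p₁) + p₂(1 − p₂))/n), the chance of rejecting is approximately Φ((p₁ − p₂ − 1.96 SE₀)/SE₁) plus the small opposite tail.

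Worked case, *r* = 0.20, *s* = 0.70: p₁ = 0.18, p₂ = 0.14, SE₀ ≈ SE₁ ≈ 0.0481. Then (0.04 − 1.96 × 0.0481)/0.0481 ≈ −1.13, and Φ ≈ 0.129. The opposite tail adds about 0.003, giving 13.2%.

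| Elicited, sequential vs quadruple | True 20%: observed | Rejects | True 30%: observed | Rejects |
| --- | --- | --- | --- | --- |
| 90% vs 90% | 18% vs 18% | 5.0% | 27% vs 27% | 5.0% |
| 80% vs 90% | 16% vs 18% | 6.9% | 24% vs 27% | 8.2% |
| 70% vs 90% | 14% vs 18% | 13.2% | 21% vs 27% | 18.7% |
| 60% vs 90% | 12% vs 18% | 24.8% | 18% vs 27% | 37.5% |

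Exact binomial enumeration agrees to within about 0.2 percentage points. The rows show how the effect scales; they do not estimate what would happen in this trial. Reversing the elicitation rates would bias against sequential therapy by the same amount.

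**The case against.** The strongest reply is that most of this is silence, not error. Section 3.6 leaves recording to electronic case report forms in a system still to be developed, and those forms may hold severity and reason-for-stopping fields. That stands as a limit. A reader might infer that each effect is recorded only as present or absent, but the protocol does not say so; it only fails to ask for more. The method of elicitation is different: the protocol does state it, as a verbal interview.

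A reader might also infer that the trial cannot show intolerable effects or discontinuation at all. That is too strong. Intake above 80% is measured in the same patients at the same visit, and pill counting is allowed. What is missing is the reason for a shortfall.

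It is tempting to add that better tolerability is what justifies the 15-point non-inferiority margin. The protocol gives no rationale for the margin, so that link cannot be charged to it. Nor can the rejection rates above be read as false-positive rates of the plan: the elicitation rates are assumed, and no significance test on adverse effects is stated. At the mildest assumed difference the rate is 7–8% against a nominal 5%.

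Finally, a written checklist does not make patients unaware of their regimen, and the Methods have them warned of side effects. Their own expectations would remain. Attributing the stopping of a drug to an effect is likewise an unblinded judgement. Both points stand, which is why the stopping item belongs beside the individual rates as a supporting measure.

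**Conclusion.** The point holds as a minor weakness of a secondary endpoint. The adverse-effect comparison relies on interviews by people who will in practice know the arm, in a trial that has declared which regimen it expects to be easier to take, so differential questioning is a credible source of bias. Its size and direction cannot be derived from the document. The protocol also does not call for severity or for whether an effect led to stopping a drug. On its own planning rates, that leaves about 46 quadruple and 23 sequential patients with low intake and no requested explanation.

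The conclusion rests on one inference, that open-label staff checking compliance know the regimen, and on the protocol as shown; a case report form not seen could already fill the second gap. Although the Methods put safety in the primary objective, adverse effects are listed as a secondary endpoint. The breath-test endpoint and the planned 258 patients are untouched.

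**What to change.** At the existing seven-day visit, have every patient complete the same one-page written checklist of the nine listed effects before speaking to staff. The wording should be identical in both arms and the answers not altered afterwards. For each effect, ask severity (mild, moderate, severe) and whether any study drug was stopped because of it. State in the protocol that the checklist is the source for the adverse-effect comparison, and report stopping a study drug because of an effect beside the individual rates as a supporting measure.

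Staff should still follow up clinically important answers, such as seizures, neuropathy and allergic reaction, and record that follow-up separately. Section 3.5 and the Methods should also agree on who conducts the visit, since one names a research staff member and the other a physician.

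The cost is one form and a few case report form fields at a visit already scheduled; treatment, visits and sample size do not change. The downside is that a checklist is likely to raise reports of mild effects in both arms, and that patients' knowledge of their regimen remains a source of bias.
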